### Intervention and comparison

#### Experimental group: Safeguarding Children Assessment and Analysis Framework (SAAF)

The SAAF assessment tool asks social workers to make a judgement relating to each of 55 items that social workers should consider when making their assessments:

 For 33 items these are judgements of level of risk or concern (both terms are used), covering the child’s developmental needs, parenting capacity and family and environmental factors. Whilst explicitly not a score card, social workers are asked to rate each item on a five-point Likert-type scale, one end of which represents ‘low level of concern’ and the other ‘high level of concern’. For 22 items these are judgements about prospects for intervention, covering parenting capacity, family and environmental factors, and child’s developmental needs. Again, this is not a score card. Social workers are asked to indicate where, again on a five-point scale, they judge the prospects for (successful) intervention to lie, with ‘reasonable prospects of success’ at one end, and ‘poor prospects’ at the other.

Social workers are then asked to make three summative judgements, using a three-point scale:Level of harm (low, moderate, high);Level of risks of re-abuse or likelihood of future harm (low, moderate, high level of risks); andProspects for successful intervention (poor, moderate, better prospects).

This is then used as a basis for guiding decision-making.

The SAAF approach to assessment and analysis will be taught to social workers in the experimental arm in a two-day training course by SAAF’s developers - *Children and Families Training*. Social workers who attend SAAF training will receive the following:

 A two-day training course aimed at improving understanding of how best to approach the task of complex assessments. The training includes:helping social workers to distinguish between the *collection* of relevant information on each of three assessment domains (Child's Developmental Needs, Parenting Capacity, and Family and Environmental Factors) and *hypothesising* how particular data might be relatedinstructing social workers on the use of a series of grids to structure and critically appraise information, with particular reference to estimating the risk to the child if nothing is done, what needs to change in order to safeguard the child, and what interventions are best placed to achieve those outcomes, and estimates of parents’ capacity to change and their willingness to engage with an appropriate protection plan Materials to further develop their competence, and support their use of the SDM tool including:▪ SAAF User Guide▪ SAAF Instruments Record▪ A book about SAAF produced by its developers [6], and▪ Access to resources on Children and Family Training’s website SAAF grids, transposed from paper to an electronic format to facilitate their use Limited post-training telephone consultancy, delivered by the trainers (Child and Family Training) to discuss problems and issues that might have emerged

The SAAF tools and training are designed to improve the *quality* of the assessments produced, and not to replace policies, practices or proformas already in use within the participating departments. Social workers using SAAF may append or use information from additional tools or sources of information, but they will continue to use the forms required by their employer, and adhere to any other policy or procedure.

#### Control group

‘No treatment’ is not an option when children are referred to CSDs because of concerns about risk of harm or inadequate parenting. The control condition will therefore be ‘management as usual’. Social workers in the control arm will continue to follow departmental policy and undertake S47 enquiries and complex assessments associated with both S47 and S17 (Assessment of Children in Need) cases, developing Child Protection Plans (CPP) as usual, supported by relevant policy guidance and management systems.

### Outcomes

#### Primary outcome

Differences between the two arms in the proportion of cases resulting in maltreatment or recurrence of maltreatment following the completion of an assessment (S17 cases) or initial child protection conference (S47 cases).

*Measures*: using administrative data (CIN data^b^) collected by LA CSDs we will assess the (re)occurrence of maltreatment, as defined by:

 Number of children who become subject to a CPP for a second or subsequent time (or for the first time following a S47 or S17 assessment that did not result in a CPP), as a result of concerns linked to the original assessment; Number of reassessments or re-referrals as a result of concerns linked to the original maltreatment/perceived risk of maltreatment;

At a national level, the CIN data include items such as ‘Initial category of abuse’ and ‘Latest category of abuse’. In order to determine whether or not the trigger incidents are related, that is are indicative of a failed plan or inadequate assessment, data are needed that provide information at a more granular level than that typically collected for the National Statistics Office (the annual CIN return^c,d^). For this purpose we will use the more detailed data gathered by the CSDs (information management) and collect data immediately post-assessment from social workers *via* an electronic questionnaire (the Case Report Form). These data will provide us with information about the concerns of social workers, their confidence in their assessments, their plans and assessments of future risk. They will also ensure that i) we do not miscategorise apparently unconnected events that in fact have a common underlying cause. For example, physical abuse by a parent and sexual abuse by a stranger *may* be unrelated, but they may also be symptoms of a seriously neglectful environment; ii) we can link children who move between one form of assessment or focus to another; for example, S17 to S47, and monitor associated changes in assessment.

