**Table 1 Tab1:** **Scenario planning - power calculations undertaken to inform the sample size**

Scenario	Re-abuse Rate % Control	Re-abuse Rate % SAAF	Unclustered total sample size	Design effect	Clustered total sample size (rounded)
1	50	40	800	1.5	1,200
2a	25	15	510	1.5	770
2b				2.0	1,000
3a	10	5	900	1.5	1,300
3b				2.0	1,800
4a	10	2.5	400	1.5	600
4b				2.0	800
5a	20	10	400	1.5	600
5b				2.0	800

Given the uncertainties in the CIN data, and in the absence of an existing, secure ICC from other studies, we judged that a design effect of 2.0 was most appropriate given the rate of repeat CPPs. This points to the need for an achieved sample size of 1,800 cases, which we estimate will be achieved within a 6-month period following the training of the experimental social workers in each CSD.

The design of the study, including reliance on administrative data, attenuates the need to factor dropout into the calculations.

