### Assignment of interventions

*Sequence generation*: social work teams within participating LAs will be randomly allocated to one of the two study arms. The allocation will be achieved by computer generated random numbers by the Northern Ireland Clinical Trials Unit (NI CTU) using randomly permuted blocks.*Allocation concealment*: the NI CTU will inform the PI and Trial Manager of the allocation of each social work team. The Trial Manager will then Email the designated contact person in each CSD to inform them of their allocation.The Trial Manager will also inform Children and Family Training, who will then liaise directly with the CSD to arrange training for those social workers/teams in the experimental arm.*Implementation*: the allocation to the intervention or control arm will be generated by the NI CTU and conveyed securely to the Trial Manager and PI.*Check on baseline equivalence*: all social workers will complete a baseline questionnaire prior to randomisation, which will provide information on their experience, training to date, expectations of the training, attitudes towards the trial, and so on. This will provide some indication of baseline equivalence between the two arms, as well as informing the interpretation of the study results.*Blinding*: given the nature of the intervention, the data to be collected, and the interface with the Trial Manager (who will be the point of contact for enquiries regarding data collection), it will not be possible to maintain the concealment of allocation, that is social workers will know whether or not they have been trained. Further, the Case Report Form will include questions about the use of the SDM tools (which the control group social workers will not be using) and the assessments that will be quality assessed may include indications that the authors were in receipt of training/used the SAAF SDM tools.

However, we will endeavour to select assessments for audit without divulging the arm from which they were sourced to those conducting the quality assessment. Each CSD will be asked to provide between 25 and 40 assessments, randomly selected by the NI CTU, from participating social workers in each arm, and make these available to the researchers undertaking the quality audit, without divulging which teams the authors belong to.

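### Whether a later event counts as a primary outcome is judged partly from a form that shows the arm, and masking is described only for the secondary quality audit

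*Protocol article*

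**What the plan says.** In the Primary outcome section, relatedness is part of the event definition. A second or first CPP counts when it arises "as a result of concerns linked to the original assessment". The other measure is "Number of reassessments or re-referrals as a result of concerns linked to the original maltreatment/perceived risk of maltreatment".

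The same section says the national Children in Need return is too coarse to settle this. It gives the purpose of the finer data as follows: "In order to determine whether or not the trigger incidents are related, that is are indicative of a failed plan or inadequate assessment". It names two sources: "For this purpose we will use the more detailed data gathered by the CSDs (information management) and collect data immediately post-assessment from social workers" by electronic questionnaire, which is the Case Report Form. Of the form it says: "These data will provide us with information about the concerns of social workers, their confidence in their assessments", and that it also covers plans and views of future risk. The section leaves room for judgement. It wants events that look separate to be recognised as related where they share a cause, and its example is two different kinds of abuse that may both stem from neglect.

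Under Assignment of interventions, the blinding paragraph says that social workers will know whether they were trained and that "the Case Report Form will include questions about the use of the SDM tools", which control workers will not be using. The masking steps described there and under Secondary outcomes all concern the audit of assessment quality. The Discussion calls the source of the primary outcome data administrative.

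**The concern.** A repeat CPP taken straight from a department's system is recorded in the same way in both arms. A repeat CPP that counts only if someone judges it related to the first assessment is a different outcome. Its value depends on what was written at the first assessment and on who reads it.

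Arm can enter by two routes. First, the form shows whether SAAF tools were used, so a person deciding linkage with the form in hand can see the arm. The article also treats relatedness as a sign that the plan or assessment failed, so that person comes close to judging the intervention itself. Second, SAAF trains workers to structure information and to consider how findings are related. It may therefore change the record against which later events are matched, even for a masked reader.

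At stake is the between-arm comparison on the primary outcome. Unequal recognition of links could create a difference where none exists, or shrink or inflate a real one.

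**Working it through.** **Plan's own figure.** Table 1, scenario 3b: 10% control v 5% SAAF, unclustered total 900, design effect 2.0. 900 × 2.0 = 1,800, as stated. The article does not state alpha or power. Assuming two-sided 5% and 80% power, the unclustered total is 870, or 948 with continuity correction, so 900 is plausible as a rounded value. At 450 per arm the power for 10% v 5% is 81.4%.

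**Inputs for the illustration.**
- Effective size: 1,800 / 2.0 = 900, or 450 per arm (equal allocation assumed).
- True rate of linked events: 10% in control (Table 1, scenario 3).
- Share of true links recognised: assumed throughout.

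**Formulas.** Observed rate = true rate × share recognised. With d = pS − pC and p̄ the mean of the two rates, se0 = √(2p̄(1 − p̄)/450) and se1 = √((pC(1 − pC) + pS(1 − pS))/450). Rejection probability = Φ((d − 1.96·se0)/se1) + Φ((−d − 1.96·se0)/se1).

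**Main illustration, no true effect.** Control 0.10 × 0.70 = 7.0%; SAAF 0.10 × 0.85 = 8.5%.
- Ratio 8.5/7.0 = 1.21. With the shares reversed, 7.0/8.5 = 0.82.
- d = 0.015, p̄ = 0.0775, se0 = 0.01783, se1 = 0.01782, d/se0 = 0.84.
- Rejection probability = Φ(−1.12) + Φ(−2.80) = about 13%, against a nominal 5%.

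**Range of assumed recognition shares.** The middle two columns take 10% true in both arms. The last two take the planned 10% v 5%.

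| Control / SAAF recognised | Spurious difference, SAAF − control | False rejection | Observed risk ratio (true 0.50) | Power |
|---|---|---|---|---|
| 100% / 100% | 0 points | 5.0% | 0.50 | 81.4% |
| 90% / 100% | +1 point | 8.0% | 0.56 | 65.3% |
| 80% / 100% | +2 points | 18.2% | 0.625 | 44.6% |
| 70% / 100% | +3 points | 36.5% | 0.71 | 24.3% |
| 100% / 90% | −1 point | 8.0% | 0.45 | 89.0% |
| 100% / 80% | −2 points | 18.2% | 0.40 | 94.3% |

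In the last two rows the higher power comes from an exaggerated benefit. The table treats only missed links. Unrelated events wrongly counted as linked would be a further error that is not modelled here.

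**The case against.** The case against has several sound parts.

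- The form is not the only evidence. The departments' detailed records are named first, and they exist for both arms.
- The form is completed immediately after the assessment, before any later event. Workers supply material for the linkage decision. A reader might infer that they make it, but the article does not say so, and it does not say that whoever decides will see the arm.
- A reader might infer that a case without a form cannot be classified. The text does not support this: the departmental records remain, and Treatment of missing data foresees missing cases and items.
- A reader might take the plan to say that administrative data remove the drop-out problem. Its claim is weaker: "reliance on administrative data, attenuates the need to factor dropout into the calculations".
- A reader might infer that SAAF records necessarily list more concerns because the tool has 33 rated items. Those ratings run from low to high concern, and a low rating does not list a concern. That SAAF changes what is recorded is a possibility only.
- A reader might infer that the list of index cases comes from returned forms. No section says so, and the intention-to-treat section commits to all cases as randomised.
- The sensitivity section promises reruns under other outcome definitions, and the abstract states the CPP indicator without a linkage condition.
- A full protocol or analysis plan may add masked linkage.

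These points narrow the concern but do not remove it. The article itself fixes a discretionary linkage criterion, a source that reveals arm, and masking described only for a secondary outcome. The promised reruns name neither the unlinked outcome nor its role.

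**Conclusion.** The concern holds in a limited form. As the article stands, classification of the primary outcome is open to error that depends on arm, through sight of the arm or through a difference in what is recorded. The direction is unknown. Fuller SAAF records could produce more links, or could let more events be judged unrelated.

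The size cannot be established from the documents, because every recognition share above is an assumption. The 70% v 85% case shifts the difference by 1.5 points, against a planned difference of 5 points. It would not usually reach significance by itself, but it raises false rejection to about 13%. Wider gaps matter more. These figures also rest on a design effect of 2.0, equal arms and a normal-approximation test. The finding is an avoidable exposure of the primary outcome. It does not show that bias will occur.

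**What to change.** 1. Decide linkage by a fixed written rule, applied by existing study staff who are unaware of arm, on an extract from which arm, team and all SAAF or decision-tool fields have been removed. Give priority to departmental data available on the same basis in both arms. Masking alone does not remove differences in the content of the records, so this priority and step 2 are both needed.
2. Name in advance, as the key analysis under Sensitivity analysis, the purely administrative outcome: any qualifying CPP within 12 months of the index assessment, linked or not. Report it beside the primary result and explain any disagreement.

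The cost is a small data-preparation step before linkage and one more analysis of data already requested. The drawback is that the unlinked outcome is diluted by unrelated events, so it should inform the reading of the primary result and not act as a veto on it.

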#### Secondary outcomes

Quality of assessments undertaken using SAAF:

High quality assessments are necessary but not sufficient for minimising the chances of (repeat) maltreatment. Other factors, such as missing information (that could not have been available to the social worker), changes in circumstances, the lack of appropriate services, or disagreement amongst professionals, may result in future maltreatment following an assessment that a child is not in need of protection (S17) or the implementation of a CPP (S47 cases). An assessment of the impact of SAAF on the quality of assessments, independently of outcomes, is therefore included in this study.

When 1,800 complex assessments have been completed, the Clinical Trials Unit will randomly select 10% of assessments, stratified by study arm and size of CSD. These 180 assessments will then be quality assessed by members of the research team, blind to whether the assessment is from the experimental or control arm of the study. It is not possible to blind the assessors to CSD given the forms used in each department. The researchers will be asked to record any information that might lead them to believe they know the arm from which the assessment was drawn; for example, reference to SAAF.

*Measures*:

 Data relating to the quality of assessments will be recorded using a quality assessment schedule developed for this study. This requires the assessor to collect information on 44 items related to assessment quality. For 30 items the responses are simply ‘yes’ (score 1) or ‘no’ (score 0). For example, item 27 asks: ‘Does the assessment make clear the changes required in the child’s care to make the child/ren safe?’, and the responses open to the assessor are: ‘Yes, the assessment makes clear the changes required in the child’s care to provide them with adequate parenting’ or ‘No, the assessment fails to makes clear the changes required in the child’s care to provide them with adequate parenting’. For the remaining 14 items there are 3 possible responses, reflecting the factor being assessed; for example, item 24 asks: ‘If included, is there evidence that, in reaching their problem formulation, the author considered other, plausible explanations?’ and the assessor is asked to select from the following 3 responses, scored respectively 2,1,0: ‘The assessment provides evidence that the social worker considered alternative theories that might explain how the present situation has come about, and has provided reasons why s/he favours the one put forward’; ‘The assessment provides no evidence that the social worker considered alternative theories that might explain how the present situation has come about, but s/he provides reasons why/evidence for the hypotheses being proposed’; ‘The assessment provides no evidence that the social worker considered alternative theories that might explain how the present situation has come about, and no reason/evidence for the hypotheses being proposed’. The maximum possible score for any assessment is 48. This is not a validated tool, but it is based on factors known to be associated with quality assessments. Whilst SAAF is designed to improve assessment and analysis, the tool is not biased towards the content of SAAF. Researchers will be provided with a user guide, which provides guidance on what is being looked for, and how to score items. For example, in relation to item 24 (above) about problem-formulation, the user guide states: ‘*Research indicates that premature conclusions can lead to mistakes, some of which can be fatal. It is good practice to consider alternate explanations or theories, and to be able to articulate why one has opted for one particular explanation theory, rather than another*’. The schedule will be piloted, the findings discussed, and re-piloted, until a satisfactory rate of inter-rater reliability is achieved. Assessors will receive training in the tool, and will be required to attain a satisfactory reliability rating before assessing SAAF and control assessments. Information gathered from social workers on their approach to assessment, information collected and their confidence in the assessment and, where relevant, the proposedCPP.2.Relationships between SAAF assessment judgements (55), overall assessments (3) and child protection plans/interventions.

In the review that identified SAAF as a promising tool to improve social work safeguarding assessments [4], the authors emphasise the importance of assessing the reliability and validity of the SAAF as a ‘tool’ to improve the classification of risk and the development availability of evidence-based programmes for those families assessed using SAAF.

We cannot directly address issues of inter-rater reliability within the resource constraints of the current project, but we will investigate:

 the extent to which the structured approach (55 judgements) is linked to the 3 summative assessments of harm, risk and prospects for intervention; to recorded variations in CPPs, and to the primary outcome. the extent to which the three summary judgements are linked with subsequent maltreatment or its absence.

Data relating to the 55 judgements and 3 summative judgements used in SAAF will be obtained directly from the SAAF forms used by social workers in the experimental arm, and from the Case Report Forms.

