We will also include a question on the quality assessment schedule that will enable assessors to indicate whether or not the assessment led them to believe it had been undertaken by a social worker in the SAAF (experimental) arm.

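### The quality audit is called blind, yet the protocol accepts that some files may reveal SAAF and plans only to record it; masking explicit mentions in both arms is a cheap improvement

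*Protocol article*

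**What the plan says.** In the protocol article, Secondary outcomes, once 1,800 complex assessments are complete "the Clinical Trials Unit will randomly select 10% of assessments, stratified by study arm and size of CSD". Then "These 180 assessments will then be quality assessed by members of the research team", and the raters are described as "blind to whether the assessment is from the experimental or control arm of the study". The section adds two qualifications. The first is that "It is not possible to blind the assessors to CSD given the forms used in each department". The second is that "The researchers will be asked to record any information that might lead them to believe they know the arm from which the assessment was drawn", with a mention of SAAF given as the example.

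Assignment of interventions (Blinding) is more cautious. It says that "the assessments that will be quality assessed may include indications that the authors were in receipt of training/used the SAAF SDM tools", and it presents the withholding of arm as something the team will try to do. Each CSD passes on the selected documents without naming the authors' teams. The schedule also carries a question on which assessors can "indicate whether or not the assessment led them to believe it had been undertaken by a social worker in the SAAF (experimental) arm".

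The schedule has 44 items, 30 of them yes/no and 14 with three response levels. The article says plainly that it is unvalidated. Raters receive a user guide and training, and must reach a satisfactory reliability rating before they score trial documents.

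**The concern.** Assessment quality is measured by readers' judgement of a narrative document, and the article describes a blinded assessor for no other outcome. If the text tells a reader that the author used SAAF, withholding the arm label does not keep that reader blind. Recording the cue documents the unmasking but does not prevent it.

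Three features make expectation plausible as a source of bias:

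- the raters belong to the trial's own research team;
- the schedule is unvalidated;
- some items call for judgement, for example whether the author weighed alternative explanations.

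A shift in scoring on recognised files passes into the arm difference in proportion to how much more often files are recognised in one arm than in the other. It is hard to undo afterwards: excluding recognised files would tend to remove the SAAF-arm assessments in which use of the tool is most visible.

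**Working it through.** **1. The plan's own figure.** 10% of 1,800 = 0.10 × 1,800 = 180. This reproduces. The claim disputes no number, so the main check is of the text.

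**2. What each stated safeguard does about revealing content.**

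| Safeguard | Where stated | Removes SAAF content from the document? |
|---|---|---|
| Random selection by the trials unit | Secondary outcomes | No |
| Arm and team withheld at release | Assignment of interventions | No; hides the label only |
| User guide, fixed response options, piloting, reliability threshold | Secondary outcomes, Measures | No; promotes agreement and narrows discretion, but raters who share an expectation can still agree |
| Rater notes any cue | Secondary outcomes | No; records it |
| Question on believed arm | Assignment of interventions | No; records it |

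No stated step acts on the content itself.

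**3. Direction of the cues.** SAAF content is expected mainly in SAAF-arm files. It need not be confined to them: Multilevel models plans an analysis of SAAF-trained workers present in the control arm and of untrained workers in the experimental arm.

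**4. Illustration of size.** The documents give no score SD, no recognition rate and no rater shift, so every input here is an assumption:

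- 90 files per arm (an equal split of 180) and no true effect;
- shares f1 and f0 of SAAF and control files recognised as SAAF;
- a mean shift of b SD on recognised files;
- design effect DE of 1 or 2.

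Formulae:

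- bias in SD units: d = (f1 − f0) × b
- standard error in SD units: √(2 × DE / 90) = 0.149 for DE = 1 and 0.211 for DE = 2
- error rate of a two-sided 5% test: 1 − Φ(1.96 − d/SE) + Φ(−1.96 − d/SE)

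| f1 − f0 | b | d | Error rate, DE = 1 | Error rate, DE = 2 |
|---|---|---|---|---|
| 0.25 | 0.2 | 0.05 | 6.3% | 5.6% |
| 0.25 | 0.3 | 0.075 | 7.9% | 6.5% |
| 0.50 | 0.3 | 0.15 | 17.2% | 11.0% |
| 0.50 | 0.5 | 0.25 | 38.9% | 22.0% |
| 1.00 | 0.5 | 0.50 | 91.8% | 66.0% |

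The last row is an extreme. The second row also covers the case where half of SAAF files and a quarter of control files are recognised: (0.50 − 0.25) × 0.3 = 0.075. The table shows that the result ranges from negligible to serious, depending on inputs that the documents do not supply.

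**The case against.** The strongest reply is that the limitation is disclosed and partly handled. Secondary outcomes foresees the cue soon after using the word blind, and Assignment of interventions concedes the limit openly. Narrative reports are hard to mask fully, and recording unmasking is a recognised response. The scoring guide, the yes/no format of most items and the reliability threshold all narrow the room for leniency, and the article states that the schedule does not favour SAAF's content. All of this stands. It makes the fault an unqualified description and a weak safeguard, not concealment.

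A reader might infer several stronger points that the documents do not support:

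- **That audited files arrive with SAAF content as a rule.** The wording is conditional. SAAF users keep their employer's forms, and SAAF judgements are to be taken from the SAAF forms and Case Report Forms.
- **That SAAF grids are attached to the audited documents.** The article says "Social workers using SAAF may append or use information from additional tools or sources of information", which does not clearly refer to the grids.
- **That only SAAF-arm files can carry a cue.** The planned analysis of trained workers in the control arm contradicts this.
- **That the believed-arm question is wrongly placed.** The article does not give its position. Form layout, like any analysis by believed arm, can sit in the full protocol, user guide or analysis plan, none of which is shown.
- **That raters favour SAAF.** No allegiance is stated, and SAAF was developed and is taught by a separate provider.

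A redaction step could also exist in a document not shown. Even so, the concession in Assignment of interventions concerns the very assessments to be quality assessed, so the audit's description should be made consistent with it.

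**Conclusion.** The point holds in a limited form. The article calls the audit blind, accepts elsewhere that content may reveal the arm in some files, and states no response to that content beyond recording it. This leaves a secondary outcome open to rater expectation bias, with cues mainly but not exclusively in SAAF-arm files.

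The size is unknown. The error rates shown, about 6% to 39% without clustering apart from the extreme row, rest wholly on assumed recognition rates, shifts and an equal split, and they take leniency as the direction. They show that modest leniency could matter with 180 documents, not that it will. No particular bias in points or SDs can be attributed to this trial, and nothing here bears on the primary outcome. The change is worth making because it is cheap and improves on record-only handling.

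**What to change.** - **Mask at release.** When the roughly 180 selected documents are prepared for the raters, obscure explicit mentions of SAAF, its training provider and any other named assessment tool or training. Use the same procedure in both arms, so that the masking is not itself a cue. Leave the analytic content in place: detaching grids or other analysis could remove genuine assessment work and bias scores against SAAF.
- **Score, then guess.** Have raters finalise all item scores before answering the believed-arm question, and require an answer for every document.
- **Report it.** Tabulate believed arm by actual arm alongside the quality result.
- **Describe it accurately.** Call the audit partially masked in Secondary outcomes, in line with Assignment of interventions.

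The cost is a small amount of preparation at a step that already exists, plus control over when one question is answered. The sample is drawn only after 1,800 assessments are complete, and at publication data collection had begun in one of the six CSDs, so there was time for the change. Masking words cannot hide a SAAF-shaped structure or style of reasoning, so some recognition will remain; the believed-arm table would help show how much.
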